### 3.3. Safety Evaluation

Adverse events (AEs) due to electroacupuncture treatment include the following: (1) possible adverse electroacupuncture treatment reactions, such as ecchymosis, fainting, and pain. (2) Aggravation due to excessive acupuncture stimulation. Researchers will classify AEs into three levels based on their severity: mild, moderate, and severe or medically significant. Researchers will evaluate these AE data from the perspectives of severity and causality. All AEs will be recorded in the CRF in detail, including severity, duration, relationship with research and treatment, severity grade, treatment, and outcome. Once any serious AE occurs, we will discontinue the participant’s treatment and decide whether to continue the study.

## 4. Sample Size Calculation

This study was a multicenter, randomized, single‐blind, controlled clinical trial, in which the primary outcome was migraine days and attacks during Weeks 9–12 vs. baseline. According to the preliminary test results derived from an internal, unpublished pilot observation conducted by our research team between April 2024 and August 2024, which involved 15 participants in each group, of the research group, the mean and standard deviation of migraine days in the electroacupuncture group and the sham electroacupuncture group were 3.13 ± 1.77 and 1.98 ± 1.46, respectively. The mean and standard deviation of migraine attacks in the electroacupuncture group and sham electroacupuncture group were 2.13 ± 1.12 and 1.17 ± 1.20, respectively. Setting the ratio of the electroacupuncture group to the sham electroacupuncture group as 1:1, the test level *α* = 0.05 (bilateral), and power (1−*β*) = 0.90, the sample size of each group was calculated to be 51 cases. Considering a shedding rate of 15%, 60 cases will be taken in each group and 120 cases in total.

## 5. Randomization

The study will use the block randomization method. Each center competes to be included in the group. The random scheme for the study is generated by the “Proc plan” program of SAS 9.4 statistical analysis software, and the random distribution cards are made, which are sealed with an opaque envelope. The envelope serial number is the same as that of the card. The envelope will be opened in the order of visits by participants. The corresponding researchers at each center will randomly assign participants into two groups based on the contents of the envelope card in a 1:1 ratio: eligible participants to the electroacupuncture group or the sham electroacupuncture group.

## 6. Blinding

Participants, efficacy evaluators, data analysts, and statistical analysts will not be aware of the grouping status of the subjects, in addition to the acupuncturists. To ensure the success of blinding, participants will be requested to restrict communication of the treatment condition and visit the hospital according to the appointment. Patients will receive treatment in the supine position at independent clinics or with screens. All participants will be requested to wear eye masks to avoid seeing the needles visually. Similarly, evaluators who do not know the grouping status will evaluate and record the observed indices. Statistical analysis using the blind method will be performed by a third party to ensure the authenticity of the research results. In addition, all researchers will receive professional training about the specifications of the research and be requested to maintain the separation of departments. In addition, the questionnaire will be administered after treatment to evaluate blinding. Participants will need to answer the question of “what kind of treatment do you think you have received?” and they will choose the answer from “electroacupuncture, sham electroacupuncture, and unclear. Bang’s Blinding Index will be used for blind evaluation.

## 7. Analysis

Data collection and entry for this study will be conducted by specially trained clinical staff. Efficacy analyses will be performed on both the intention‐to‐treat (ITT) population and the per‐protocol set (PPS) population. Missing values for patients in each group will be imputed using the last observation carried forward (LOCF) method. The safety analysis set (SAS) will be analyzed within the ITT population, which includes all randomized subjects who received at least one treatment.

Given that additional acupoints are selected based on the specific location of headache during acute attacks, we will quantitatively report the percentage of patients in each subgroup and compare baseline characteristics and changes in primary outcomes across subgroups.

SAS software (Version 9.4; SAS Institute Inc., Cary, North Carolina 27513, US) will be used for the statistical analysis. Qualitative data will be described as cases and percentages, and quantitative variables will be described as mean, median, standard deviation, and quartile range. Statistical significance was set at *p* < 0.05.

The primary outcome of this study was migraine days and attacks during Weeks 9–12 vs. baseline. The data will be recorded in a headache diary and analyzed using two independent sample *t*‐tests or rank‐sum tests. For the analysis of secondary outcomes, two independent sample *t*‐tests or rank‐sum tests were used for quantitative data, and the chi‐square test or Fisher’s exact test will be used for qualitative data. Data obtained from repeated measurements will be statistically analyzed using generalized estimating equations. The chi‐square test will also be used for a safety indicator.

The headache diary in this study involved multiple data collections. If participants complete the headache diary for at least 28 days in consecutive 4‐week periods, researchers will directly calculate the number of migraine days per month. If the number of days that participants complete the headache diary in consecutive 4 weeks is less than 20, monthly migraine days will be classified as missing. Missing days will be defined as days in which participants do not complete the evening report and do not report headaches. Estimation over 4 weeks will be used for missing data, using the number of migraine days within four weeks divided by the number of days observed during four weeks multiplied by 28 as the monthly score for the four weeks.

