### 3.1. Primary Outcome

The primary outcome was migraine days and attacks during Weeks 9–12 vs. baseline. Data were recorded in a headache diary.

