### 3.2. Secondary Outcomes (All vs. Baseline Unless Specified)

The secondary outcomes included the following:1.Frequency‐related: migraine days/attacks per 4 weeks (Weeks 1–24, excluding Weeks 9–12; and during menstrual/nonmenstrual periods).2.Symptom characteristics: days/attacks with migraine‐associated symptoms (nausea, vomiting, photophobia, and phonophobia) and attack duration per 4 weeks.3.Patient‐reported: (a) VAS: The VAS score is derived from the headache diary, which will be evaluated during the 4‐week baseline period and Weeks 1–24. (b) MIDAS [25]: This is a questionnaire used to assess the degree of migraine‐related disability and reflect the severity of migraine. The questionnaire is simple and effective and has been widely recognized and accepted by scholars worldwide. It was translated into Chinese in 2006 and has good test–retest reliability and validity. This will be evaluated at Weeks 0 and 12. (c) Insomnia Severity Index (ISI) [26]: It evaluates the severity of subjective insomnia in patients over the past week, including seven items, each with 0–4 points. The higher the score, the more serious the degree of insomnia. This will be evaluated at Weeks 0 and 12. (d) Generalized Anxiety Disorder‐7 (GAD‐7) (Copyright 1999 Pfizer Inc., all rights reserved) [27]: This scale is commonly used to evaluate generalized anxiety disorder. The scale evaluates the frequency and severity of anxiety symptoms in the past 2 weeks through seven questions. This will be evaluated at Weeks 0 and 12. (e) Patient Health Questionnaire‐9 (PHQ‐9) (Copyright 1999 Pfizer Inc., all rights reserved) [27]: It is a simple and effective self‐rating scale for assessing whether individuals have depressive symptoms and their severity. It consists of nine questions covering common symptoms of depression. This will be evaluated at Weeks 0 and 12.4.Others: treatment response rate (the proportion of patients with a reduction of ≥ 50%, 75%, or 100% per four weeks migraine days compared with baseline [28]), average dosage, and frequency of emergency drugs.

The above data regarding MRM days, attacks, duration, associated symptoms, VAS scores, and usage of remedial drugs were all derived from the headache diary. The participants will be required to complete a headache diary for at least 20 of the 28 days [29].

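### LOCF lets an earlier 4-week count stand in for a missing Weeks 9–12 window, which can bias the primary comparison when loss differs between arms

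*Protocol article*

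**What the plan says.** All of this is in the protocol article.

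- Section 3.1 sets the endpoint in the last treatment window: "The primary outcome was migraine days and attacks during Weeks" 9–12, compared with baseline.
- Section 7 names the primary test: "The data will be recorded in a headache diary and analyzed using two independent sample" t-tests, or rank-sum tests.
- Section 7 gives the general rule for missing data: "Missing values for patients in each group will be imputed using the last observation carried forward (LOCF) method".
- Section 7 also has a diary rule. If the number of completed days in a 4-week window "is less than 20, monthly migraine days will be classified as missing". For incomplete diaries it adds a proration: "Estimation over 4 weeks will be used for missing data, using the number of migraine days within four weeks divided by the number of days". The divisor is the count of days with diary data, and the result is scaled up to 28 days.
- Section 7 adds a method for longitudinal data: "Data obtained from repeated measurements will be statistically analyzed using generalized estimating equations". It does not name this as the primary analysis.
- Section 4 plans for 15% dropout overall and does not split it by arm.

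The article does not spell out the order of the two missing-data rules. The natural reading is that windows with 20 to 27 diary days are prorated and windows below 20 are missing. After withdrawal there are no observed days to prorate from, so LOCF is all that remains.

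**The concern.** The endpoint is a late-window change in a treatment given over three successive 4-week windows. If patients improve gradually, a count from Weeks 1–4 or 5–8 shows less improvement than the same patient would have shown in Weeks 9–12. Carrying it forward pulls that patient's change towards zero.

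The arm with more missing windows is pulled further. The t-test then reads a difference in dropout as a difference in effect. This needs no link between dropout and outcome; unequal loss and a continuing trend are enough. If sham loses more patients, the bias favours electroacupuncture. If electroacupuncture loses more, it works against it. With equal loss and a real effect, the estimate shrinks. LOCF is therefore not reliably conservative.

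The method is fixed in the text, so this is a stated choice and not a detail left to the statistical analysis plan.

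**Working it through.** **The plan's own dropout figure.** 51 / (1 − 0.15) = 60 per arm, as stated in Section 4. The plan thus allows for 60 − 51 = 9 patients lost per arm.

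**Inputs from Section 4.** Migraine days are 3.13 ± 1.77 (electroacupuncture) and 1.98 ± 1.46 (sham).
- Difference: 3.13 − 1.98 = 1.15.
- Pooled SD: √[(1.77² + 1.46²)/2] = 1.622.

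**Assumptions not in the documents.**
- The pilot figures are reductions. The article does not say so, but the electroacupuncture figure is the larger one and fewer migraine days is better.
- Under no true effect, both arms have mean reductions m1 = 1.0, m2 = 1.5 and m3 = 1.98 in the three windows.
- Dropout is unrelated to outcome. The last available value is equally often baseline, Weeks 1–4 or Weeks 5–8.
- Dropout is split 10%/20% or 5%/25%; both average the planned 15%.

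**Formulas**, with p the dropout in an arm:
- *Post-baseline windows only* (patients with none are left out): mean = [m3(1 − p) + (p/3)(m1 + m2)] / (1 − p/3), with n = 60(1 − p/3).
- *Baseline may also be carried* (change 0): mean = m3(1 − p) + (p/3)(0 + m1 + m2), with n = 60.
- Rejection rate = Φ(−1.96 + δ/SE) + Φ(−1.96 − δ/SE), where δ is the false difference.

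**Results, no true effect:**

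| Dropout | Carried | Means | False difference | SE | Type I error |
|---|---|---|---|---|---|
| 10% vs 20% | post-baseline only | 1.930, 1.876 | 0.05 | 1.622√(1/58 + 1/56) = 0.304 | 5.4% |
| 10% vs 20% | baseline too | 1.865, 1.751 | 0.11 | 1.622√(2/60) = 0.296 | 6.7% |
| 5% vs 25% | post-baseline only | 1.955, 1.847 | 0.11 | 1.622√(1/59 + 1/55) = 0.304 | 6.5% |
| 5% vs 25% | baseline too | 1.923, 1.693 | 0.23 | 0.296 | 12.1% |

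**Equal 15% dropout, true difference 1.15**, with electroacupuncture reductions of 1.5, 2.3 and 3.13:
- Baseline too: (3.13 × 0.85 + 0.05 × 3.8) − (1.98 × 0.85 + 0.05 × 2.5) = 2.8505 − 1.808 = 1.04.
- Post-baseline only: 1.0425 / 0.95 = 1.10.

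**Sensitivity to the trajectory.**
- If most improvement comes early (1.5, 1.9, 1.98) and no baseline is carried, 5% vs 25% gives only 0.04 days and 5.2%.
- A simulation (4,000 trials per scenario, 60 per arm, linear improvement to 1.98, SD 1.62, within-patient correlation 0.6, baseline among the carried values) gave 0.13 days and 7.7% for 10%/20%, and 0.27 days and 14.5% for 5%/25%. Analysing only observed values in the same scenarios gave about 5%.
- In that simulation with equal 15% dropout, type I error was 4.9%. With a true 1.15, power was 90% under LOCF and 94% with observed values only.

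**The case against.** The strongest reply is that the size is assumed. The article gives no week-by-week course, and its 15% dropout is not split by arm. Participants are blinded and both arms follow the same schedule, so a fivefold difference in loss is extreme. With equal loss the test keeps its level, and the simulated power stays at the planned 90%. All of this stands. It limits the size of the problem but does not remove the mechanism.

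Some stronger readings are tempting but not supported:

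- *LOCF is the only rule for missing data.* It is not. Section 7 also prorates partial diaries, so the point covers only windows below 20 days and windows after withdrawal.
- *Baseline will be carried forward.* The article does not say so. It would arise if a patient with no usable post-baseline window stayed in the analysis. Without it, the 5%/25% error rate falls from 12.1% to 6.5%.
- *The standard errors are too small.* Imputed values do count as observed, and the simulated LOCF standard error (0.302) is about 6% below that from 51 observed per arm (0.321). But it matched the sampling SD of the LOCF estimate (0.303). The excess type I error came from bias.
- *LOCF gives wrong VAS or attack-duration values for patients who become migraine-free.* That needs attack-free windows to be coded as missing, and nothing in the article says they are.
- *A sensitivity analysis is lacking.* That may sit in the statistical analysis plan, which is not shown.

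**Conclusion.** The concern holds in this limited form. For a Weeks 9–12 window that is missing outright, the stated rule substitutes a count from earlier in treatment. That can bias the primary contrast in either direction when loss differs by arm.

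Under the assumed course, the false difference runs from 0.05 days (10%/20%, post-baseline windows only) to 0.23 days (5%/25%, baseline allowed). Against the planned 1.15 that is about 5% to 20%. The upper end needs both an extreme split and an unstated rule. An early plateau makes the bias smaller, and a steadier decline makes it larger. With equal 15% loss, the harm is a diluted estimate (1.15 to about 1.04–1.10) and not a false positive.

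The change should be made: the size is uncertain, but a better method can use windows that the trial already collects.

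**What to change.** Replace LOCF for the primary outcome. Either of these would do:

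- Fit a likelihood-based mixed model to all observed 4-week windows and report the Weeks 9–12 treatment contrast.
- Multiply impute missing windows by arm from baseline and earlier windows. Then apply the planned generalized estimating equations or the two-sample comparison, and report the same contrast.

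State in the same paragraph that proration applies to windows with 20 to 27 diary days, and that the new method applies below 20 days and after withdrawal.

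The cost is revised wording and modest programming, with no new data. The confidence interval may be slightly wider. Section 2.1 has recruitment running to May 2027, so there is time to make the change before unblinding.

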However, this study had certain limitations. To adhere to medical ethical standards, the patients were permitted to use emergency medications during the study period, which may have influenced the assessment of therapeutic efficacy. To mitigate this impact, we conducted subgroup and covariate analyses. Additionally, because of the unique nature of acupuncture techniques, the acupuncturists could not be blinded in this study.

In conclusion, high‐quality clinical studies investigating the efficacy and safety of electroacupuncture for MRM are essential. We anticipate that the results will provide clinical evidence for the use of electroacupuncture in the treatment of MRM, ultimately enhancing the clinical symptoms and quality of life of patients.

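### The only definition given for the ITT population requires at least one treatment, so as written no efficacy set is sure to keep all randomised women

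*Protocol article*

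**What the plan says.** Section 7 (Analysis) opens the description of the analysis sets with "Efficacy analyses will be performed on both the" ITT population and the per-protocol set. It does not say which of the two is primary. Two sentences later it turns to safety: "The safety analysis set (SAS) will be analyzed within the ITT population". The clause that follows supplies the only definition of ITT in the article: "ITT population, which includes all randomized subjects who received at least one treatment". No other section defines ITT, and no set of all randomised women is named.

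Three other places bear on the point:

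- **Section 5 (Randomization)** says who sees the allocation: "The corresponding researchers at each center will randomly assign participants into two groups based on the contents of the envelope card".
- **Section 9 (Discussion)** states that "the acupuncturists could not be blinded in this study". Section 6 (Blinding) is worded so that acupuncturists could be read as blinded or not, and the Discussion settles it. Section 6 is clear that participants, efficacy evaluators and analysts are blinded.
- **Table 2** places randomisation in the enrolment column (Weeks −3 to 0) and treatment from Week 1.

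For missing data, Section 7 says: "Missing values for patients in each group will be imputed using the last observation carried forward (LOCF) method".

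**The concern.** An ITT population keeps every randomised participant in the arm assigned. Requiring at least one session makes membership depend on something that happens after randomisation. That is the usual form of a safety set or a modified ITT set. The per-protocol set does not repair this, because it too is selected on events after randomisation.

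Leaving out never-treated participants does little harm when nobody who can affect the start of treatment knows the arm. That safeguard is incomplete here. The researcher who opens the envelope and the acupuncturist both know the arm, and Table 2 allows time between allocation and session 1. If women were lost in that interval at different rates, or for different reasons, in the two arms, the comparison labelled ITT would no longer be the randomised one.

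**Working it through.** **1. The plan's own figure.** The point disputes no number, but the denominators should be fixed first. Section 4 gives pilot migraine-day figures of 3.13 ± 1.77 (electroacupuncture) and 1.98 ± 1.46 (sham). It sets "0.05 (bilateral), and power" at "0.90, the sample size of each group was calculated to be 51 cases".

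- Planned difference: 3.13 − 1.98 = 1.15.
- Using the larger SD: n = 2 × (1.960 + 1.282)² × 1.77² / 1.15² = 49.8 per arm. Adding the small-sample term 1.96²/4 = 0.96 gives 50.7, so 51, as stated.
- Dropout: 51 / (1 − 0.15) = 60 per arm, 120 in total, as stated.

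**2. The definition against the numbers.** An all-randomised set has 60 + 60 = 120 women. The set in Section 7 has 120 minus those who never receive a session. The two coincide only if everyone starts. The article gives no expected number of untreated women, so the gap cannot be computed, only illustrated.

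**3. Illustration.** Assume that 3 of 60 women in one arm never start, that they would show no reduction, and that the pilot means are reductions among women who do start. Section 4 calls those means migraine days, so the last assumption is a reading of the text. If the mean among starters is m, the all-randomised mean is (57/60) × m = 0.95 m. Leaving the three out raises the arm mean by 0.05 m.

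| Where the untreated women are | Effect of leaving them out | Share of 1.15 |
|---|---|---|
| Electroacupuncture only | that arm's mean up by 0.05 × 3.13 = 0.16 days; difference larger | 13.6% |
| Sham only | that arm's mean up by 0.05 × 1.98 = 0.10 days; difference smaller | 8.6% |
| 3 in each arm | difference larger by 0.05 × 1.15 = 0.06 days | 5% |

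The direction is therefore not fixed.

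**4. Wider range.** Let k of 60 in one arm be untreated, and let their outcome differ by g days from the rest of that arm. The shift in the arm mean is (k/60) × g. With assumed k from 1 to 6 and g from 0.5 to 2.0:

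- lowest: (1/60) × 0.5 = 0.01 days (0.7% of 1.15);
- highest: (6/60) × 2.0 = 0.20 days (17% of 1.15).

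**5. Power.** With the root-mean-square SD, √((1.77² + 1.46²)/2) = 1.62, power is Φ(1.15 / (1.62 × √(2/n)) − 1.96). This gives 0.973 at 60 per arm and 0.958 at 54 per arm. Sample size is therefore not at stake; what matters is which women are compared.

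**6. The missing-data rule.** A randomised woman with no post-baseline diary has only her baseline value. LOCF, taken at its word, carries that value forward and gives her a change of exactly zero. The zero reduction assumed in step 3 is thus also what the stated rule would impute, so widening the set without settling this point would put fixed values into the primary comparison.

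**The case against.** The strongest objection is that the sentence is about the safety set. Receipt of at least one treatment is a natural safety-set condition, and the wording places that set inside ITT, so the clause may simply be misplaced. On that reading no randomised woman is lost from efficacy. ITT is merely undefined, and a journal article may leave that to a fuller document. This is plausible and cannot be excluded. It does not remove the point, because by its grammar the clause attaches to ITT and is the only definition a reader is given.

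The second objection is that participants are blinded and sham treatment uses the same acupoints and schedule. A woman cannot decline session 1 because of an arm she does not know. This stands and narrows the route to one: staff who know the allocation influencing whether she starts. The time between envelope and first session is also not given, so the opportunity may be small.

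The third objection is that all the sizes above are assumed. This also stands.

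Two stronger readings are tempting and should be resisted. A reader might infer that the trial's main efficacy set is the restricted one, but Section 7 lists ITT and per-protocol side by side and ranks neither. A reader might also infer that safety would be counted under the assigned arm even when the other device was applied. The text says who is in the safety set, not under which arm they are counted, so that does not follow.

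**Conclusion.** The point holds as a defect of definition. Taken literally, Section 7 labels a treated-only set as ITT, and no efficacy analysis is sure to retain all 120 randomised women. If the clause was meant for the safety set, the sentence still attaches it to the wrong population and must be corrected.

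The consequence is of unknown size and probably small. The illustrative shift of 0.10 to 0.16 days in one arm's mean rests on three assumptions: 3 of 60 untreated, no reduction in those women, and pilot figures that are reductions. The documents do not show that allocation-dependent loss before session 1 will occur, only that the wording would not protect the comparison if it did. The change is worth making because it removes an exclusion after randomisation at almost no cost.

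**What to change.** - Define ITT as all randomised women, analysed in the arm assigned, whether or not treated. Name it the primary efficacy set and keep the per-protocol set as a sensitivity analysis.
- Define the safety set in its own sentence as women who received at least one session.
- State how women with no post-baseline diary are handled in the primary comparison, which Section 7 plans as a t-test or rank-sum test. If LOCF is kept, say openly that their baseline is carried forward. If it is not, name the replacement.

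The cost is a few sentences and perhaps a few more records in the primary analysis. The first two changes are wording only; the third needs a decision on imputation, which should be made before the allocation is unblinded for analysis. Recruitment is planned to run to May 2027, and neither the sample size nor data collection has to change.

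### Two primary variables, migraine days and migraine attacks, are each tested at 0.05 with no rule on whether success needs either or both; if either suffices, the stated 5% error is not held.

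*Protocol article*

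**What the plan says.** Sections 3.1, 4 and 7 and the abstract all define the primary outcome as migraine days and attacks in Weeks 9–12 compared with baseline; Section 7 reads "The primary outcome of this study was migraine days and attacks during Weeks 9–12 vs. baseline". The abstract and these sections use the singular. The schedule in Table 2 and the subgroup paragraph of Section 7 use the plural.

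On the test, Section 7 says "The data will be recorded in a headache diary and analyzed using two independent sample" *t*-tests, or rank-sum tests. Each of these handles one variable at a time. On the level it says "Statistical significance was set at *p* < 0.05", with no separate provision for the primary analysis.

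Section 4 gives separate pilot figures for the two variables, electroacupuncture first and then sham. The migraine days "were 3.13 ± 1.77 and 1.98 ± 1.46, respectively"; the migraine attacks "were 2.13 ± 1.12 and 1.17 ± 1.20, respectively". With two-sided alpha 0.05 and power 0.90, "the sample size of each group was calculated to be 51 cases", raised to 60 for 15% dropout. Section 4 does not say which variable, or which SD, gave 51.

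No section contains an either/both rule, an order of testing or a split of alpha.

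**The concern.** Two variables tested separately at 0.05 give two chances of a false-positive primary result unless the plan says that both must be won. This article fixes the variables, the type of test and the level, but not what counts as a positive trial. A significant result on only one variable could then be presented as meeting the primary outcome, and whether that is enough could be decided after the results are known. At stake is whether the two-sided 0.05 in Section 4 really applies to the primary claim.

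**Working it through.** **Inputs from Section 4.** Days: difference 3.13 − 1.98 = 1.15, SDs 1.77 and 1.46. Attacks: difference 2.13 − 1.17 = 0.96, SDs 1.12 and 1.20. Two-sided alpha 0.05, power 0.90, 1:1 allocation, 51 per group. The values are labelled as days and attacks and are higher under electroacupuncture. They are taken here as reductions from baseline, which is an assumption.

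**Pooled SD and standardised difference.**
- Days: √((1.77² + 1.46²)/2) = 1.622; d = 1.15/1.622 = 0.709.
- Attacks: √((1.12² + 1.20²)/2) = 1.161; d = 0.96/1.161 = 0.827.

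**Reproducing 51.** The normal approximation is n = 2(z₁₋α/₂ + z₀.₉₀)²/d². The noncentral *t* version adds about one or two per group. Results for 90% power:

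| Variable and SD | two-sided 0.05: z / *t* | two-sided 0.025: z / *t* |
|---|---|---|
| Days, pooled 1.622 | 42 / 43 | 50 / 51 |
| Days, larger 1.77 | 50 / 51 | 59 / 61 |
| Attacks, pooled 1.161 | 31 / 32 | 37 / 38 |

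For example, days with the pooled SD at 0.05: 2(1.960 + 1.282)²/0.709² ≈ 41.8, so 42. The stated 51 is reached in two ways: days with the larger SD at 0.05, or days with the pooled SD at 0.025. The dropout step reproduces: 51/0.85 = 60.

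**Error if either variable suffices.** With both null hypotheses true, error = 1 − P(|Z₁| ≤ 1.96 and |Z₂| ≤ 1.96), where Z₁ and Z₂ are bivariate normal with correlation ρ. At ρ = 0 this is 1 − 0.95² = 9.75%. The article gives no correlation, so a range is shown:

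| ρ | 0 | 0.5 | 0.7 | 0.8 | 0.9 | 0.95 |
|---|---|---|---|---|---|---|
| Error | 9.75% | 9.07% | 8.35% | 7.81% | 7.04% | 6.46% |

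**Error if both are required.** It cannot exceed the level of either single test, so it is at most 5%.

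**Power at 51 per group, both required at 0.05.** With pooled SDs (normal approximation), days have 94.7% and attacks 98.7%. Joint power is 0.947 × 0.987 ≈ 93.5% at ρ = 0 and 94.6% at ρ = 0.9. If days are planned with SD 1.77, their power is 90.1% (*t*). Joint power with the pooled attacks figure of 98.5% (*t*) is then 0.901 × 0.985 ≈ 88.8% at ρ = 0 and cannot exceed 90.1%.

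**Power at 51 per group, two-sided 0.025 (noncentral *t*).**
- Days: 90.2% with the pooled SD; 84.1% with SD 1.77, or 90.0% if all 60 are evaluable.
- Attacks: 97.0% with the pooled SD; 96.0% with SD 1.20.
- At least one of the two at 0.025 (pooled SDs, normal approximation): 99.8% at ρ = 0 and 97.5% at ρ = 0.9.

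Holm tests the larger p-value at 0.05 once the smaller has passed 0.025, so the single-variable figures at 0.025 are lower bounds for Holm.

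**The case against.** The strongest objection is that the article never says one variable is enough. Its abstract, Section 3.1, Section 4 and Section 7 use the singular and join the variables with *and*. The literal reading is that both are needed, and then no correction is due. A reader might infer that the trial has a false-positive risk of 7–10% as a matter of fact. The text does not support that: the inflation depends on the either reading and on an assumed correlation. The top of the range is also unlikely, because both counts come from the same diary over the same four weeks.

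A second objection is that a separate analysis plan may hold the rule. That would excuse silence. Here, however, the article itself states two variables, single-variable tests and one general level. The plurals in Table 2 and in the subgroup paragraph also weaken the view that one joint claim was plainly meant. What remains is an ambiguity in a stated decision rule, not a proven inflation of error.

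A third objection is that 51 may already contain a correction, since days with the pooled SD at 0.025 need exactly 51. A reader might conclude that the planned size supports a corrected level at no cost. That does not follow either. The larger SD at the stated 0.05 also gives 51, and on that route days would need 61 per group at 0.025, above the 60 to be enrolled. Section 4 names only 0.05 and does not show its route.

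**Conclusion.** The point stands in conditional form. The article sets two primary variables and one uncorrected level, and leaves open whether either or both must be significant. If either suffices, the family-wise error is about 6.5–9.75% against the stated two-sided 0.05, for assumed correlations from 0.95 down to 0, and probably in the lower part of that range. If both are required, it is at most 5%. The defect is that the choice is not fixed in advance.

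Whether 51 per group carries a corrected level at 90% power depends on an SD choice that Section 4 does not disclose. All power figures rest on a pilot of 15 per group and on reading its values as reductions from baseline.

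**What to change.** Before unblinding, write one rule in the same words in Sections 3.1, 4 and 7, in place of the general 0.05 for the primary analysis. There are two options:

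1. **Both required.** Success means that days and attacks are each significant at two-sided 0.05. This matches the present wording and needs no alpha correction. A win on one variable alone is then not a positive trial.
2. **Either suffices, under Holm.** Test the smaller p-value at 0.025 and, if it passes, the other at 0.05, for a family-wise two-sided 0.05.

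Section 4 should then state the variable, SD and alpha behind 51, and that the pilot values are reductions from baseline, if they are.

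The cost is wording in the protocol and analysis plan. The sample size need not change under the first option with pooled SDs; with SD 1.77 for days, joint power is about 89–90%. Under Holm the downside falls on days: power at 0.025 is 90.2% with the pooled SD but 84.1% with SD 1.77, recovering to about 90% only if all 60 per group are evaluable. Attacks keep about 96–97%.
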